### Statistical analysis

Multivariate binary or multinomial logistic regression models as well as multiple linear regression models will be used to analyze the effect of birth weight (differentiated into VLBW, LBW and birth weight ≥ 2,500 g) on the outcomes. Adjustment will be made for sex, year of birth and socioeconomic status. Modification of the presumed adverse short and long-term effects of preterm birth through early psychosocial care will be analyzed by modeling the exposure to such a program as predictor for parental stress, parent-child relationship, quality of life, child development, healthcare utilization and costs. Effect modification will be explored by including the corresponding interaction-terms in the regression models. With an expected response rate of 30 % and an expected power (1-β) of 80 %, effect sizes (Cohen’s f) of 0.045 or higher can be detected at a 5 % significance level in analyses with the linked dataset (see Fig. 4). For analyses based on the whole administrative data cohort, effect sizes (Cohen’s f) of 0.035 or higher can be detected with a power of 80 % at the 5 % significance level.

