#### Hypotheses

Preterm birth and subsequent need for medical treatment disturbs the process of postnatal attachment and will have an impact on (I) parental stress, parent-child-relationship, and quality of life of family and child at age 1–7 years (primary outcomes) and (II) mental and physical child development (e.g. school performance, comorbidities), healthcare utilization and cost (secondary outcomes) during that time of life.Early psychosocial intervention that aims to support attachment and parental competency improves the parent-child-relationship and modifies the hypothesized adverse short and long-term consequences of preterm birth for the child, the child’s family, and the healthcare system.

The hypothesized causal model is shown in Fig. 1.

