## Methods/Design

EcoCare-PIn is a cohort study comprising the linkage of individual-level data from two different sources: (1) administrative claims data from the German statutory health insurance AOK PLUS on all insured children born between 2007 and 2013 in Saxony and (2) primary data collected by means of questionnaires (in 2014/2015) from parents or legal caregivers of VLBW (very low birth weight) infants (<1,500 g), LBW (low birth weight) infants (1,500 to 2,499 g), and infants with a birth weight of 2,500 g or higher as controls.

Preterm birth is generally defined as birth before 37 completed weeks of gestation [2]. As there is considerable overlap between gestational age under 37 weeks and birth weight below 2,500 g, the use of birth weight (<2,500 g) for the definition of preterm born children instead of gestational age (<37 weeks) can be regarded as an acceptable approach in case that data on gestational age are not available or of uncertain quality [40, 41]. As the AOK PLUS does not provide data on gestational age, but on birth weight, we will use the latter as proxy measure for preterm birth.

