### Design and recruitment

The study is based on pseudonymized *administrative outpatient and inpatient data* of all children born in Saxony between January 1^st^, 2007 and December 31^st^, 2013 with health insurance at the AOK PLUS. The whole cohort of newborns will include almost 140,000 children, with approximately 1,000 VLBW- and 5,500 LBW-children among them. A broad set of insurance data will be provided and analyzed within this study, including birth weight (classified into <1,500 g (VLBW), 1,500–2,499 g (LBW) and ≥2,500 g (controls)), selected sociodemographic characteristics of children (age, sex, first three digits of ZIP code), diagnoses (ICD-10 codes), diagnosis related billing information (DRG-codes), prescriptions (PZN-codes, ATC-codes, cost), medical procedures (OPS-codes), claim codes for outpatient services and procedures (EBM-codes) and data of healthcare providers (discipline, first three digits of ZIP code) [42]. Based upon these pseudonymized administrative data, we will investigate and compare VLBW-, LBW- and control children with regard to mental and physical development, healthcare utilization and cost from birth through December 31^st^, 2013.

To enable further analyses, additional *primary data* will be collected on a subgroup of the described cohort of children. With support from the AOK PLUS, parents or legal caregivers from all preterm born children and parents/legal caregivers of a matched sample of 10,000 control children will be approached via postal questionnaires. Control children for the primary data collection will be selected via frequency matching according to birth year, sex and administrative district.

The questionnaire will cover information on parental stress, parent-child relationship, child’s physical and mental development (including school performance), quality of life of children, family quality of life, sociodemographic characteristics of parents, and exposure to psychosocial care in the neonatal period. These primary data will be linked to the administrative data on an individual level.

Figure 2 provides a flow chart on the design of the study.

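### The stated adjustment set for the birth-weight models omits multiple birth, so part of any difference in parent and family outcomes may be wrongly read as a consequence of preterm birth; the size is unknown from the documents

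*Protocol article*

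**What the plan says.** The Statistical analysis section describes regression models for the effect of birth weight in three groups (VLBW, LBW, 2,500 g or more) and names the covariates in one sentence: "Adjustment will be made for sex, year of birth and socioeconomic status". The sentence is worded as a definite list. It has no 'such as' and does not refer to further variables.

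Design and recruitment gives the matching: "Control children for the primary data collection will be selected via frequency matching according to birth year, sex and administrative district".

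The Methods/Design introduction explains that the insurer holds no gestational age and says of birth weight: "we will use the latter as proxy measure for preterm birth". Under Hypotheses, the first hypothesis begins "Preterm birth and subsequent need for medical treatment disturbs the process of postnatal attachment" and gives as its first set of outcomes "parental stress, parent-child-relationship, and quality of life of family and child at age 1–7 years (primary outcomes").

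On data, Design and recruitment lists among the claims fields "selected sociodemographic characteristics of children (age, sex, first three digits of ZIP code"), followed by diagnosis, billing, prescription and procedure codes. The last questionnaire topics it lists are "sociodemographic characteristics of parents, and exposure to psychosocial care in the neonatal period". Twins or multiples do not appear anywhere in the visible text as a covariate, matching factor, exclusion, stratum or questionnaire topic.

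**The concern.** Multiple birth is settled before birth weight and lowers it. It also has its own route to the outcomes, because parents who raise two or three infants at once carry a load that a singleton's parents do not, whatever the children weighed. It is therefore a common cause of exposure and outcome. It does not lie on the path the study wants to estimate, which runs from preterm birth and medical treatment through disturbed attachment. Adjusting for it is not over-adjustment.

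The planned covariates and matching factors do not remove this. Families of the same socioeconomic status, in the same district, with a child of the same sex and birth year, can still differ in whether the child is a twin. Because birth weight stands in for preterm birth, any twin-related difference would be read as a consequence of prematurity.

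The study aims to detect very small effects, so a modest bias could decide a primary result. This is a matter of bias in the estimate. The dependence between records of twin siblings is a separate question.

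**Working it through.** **Inputs from the protocol article.** Families approached: about 1,000 VLBW, 5,500 LBW and 10,000 controls (Design and recruitment). Response 30 %, power 80 %, two-sided 5 % level, detectable Cohen's f 0.045 in the linked dataset, three exposure groups (Statistical analysis).

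**Inputs that are assumptions.** The documents give neither the share of multiples by weight group nor the effect of multiple birth on any outcome. I take a share of 10-25 % in both low-weight groups and 2 % in controls, a shift of 0.1-0.4 SD, and no true effect of birth weight.

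**Step 1: reproduce the plan's figure.**
- Responders: 0.30 × 1,000 / 5,500 / 10,000 = 300 / 1,650 / 3,000, so N = 4,950.
- Noncentral F test with 2 numerator df and noncentrality N × f²: detectable f = 0.0441 at 80 % power. At f = 0.045 the power is 81.6 %. The stated 0.045 reproduces.

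**Step 2: put f on the SD scale.**
- Low-weight share of responders: q = 1,950 / 4,950 = 0.394.
- If both low-weight groups have the same mean, f = difference × √(q(1 − q)) = difference × 0.489.
- So f = 0.045 corresponds to 0.045 / 0.489 = 0.092 SD between all low-weight children and controls.

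**Step 3: spurious difference and its consequences.** Bias = (share in low weight − 0.02) × shift; f = 0.489 × bias; rejection from the same noncentral F.

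| Share, low weight vs controls | Shift (SD) | Bias (SD) | Spurious f | Rejection at 5 % |
|---|---|---|---|---|
| 10 % vs 2 % | 0.1 | 0.008 | 0.004 | 5.6 % |
| 20 % vs 2 % | 0.1 | 0.018 | 0.009 | 8 % |
| 20 % vs 2 % | 0.3 | 0.054 | 0.026 | 36 % |
| 25 % vs 2 % | 0.1 | 0.023 | 0.011 | 10 % |
| 25 % vs 2 % | 0.2 | 0.046 | 0.022 | 27 % |
| 25 % vs 2 % | 0.3 | 0.069 | 0.034 | 56 % |
| 25 % vs 2 % | 0.4 | 0.092 | 0.045 | 82 % |

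The result runs from practically nominal to the full effect the study is powered for.

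**Step 4: price of adjustment at 25 % vs 2 %.**
- Overall share of multiples: 0.394 × 0.25 + 0.606 × 0.02 = 0.111.
- Correlation of multiple birth with low weight: 0.23 × 0.489 / √(0.111 × 0.889) = 0.358.
- Variance inflation: 1 / (1 − 0.358²) = 1.147; standard error × √1.147 = 1.07.
- Detectable f: 0.0441 × 1.07 = 0.047.

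**The case against.** **Size.** Everything beyond the structure is assumed. Multiples at 10 % against 2 % with a shift of 0.1 SD leave the test at 5.6 %; at 20-25 % and the same shift it is 8-10 %. Nothing in the documents says where the truth lies. This stands. A reader might infer from the upper rows that the study will report an effect of preterm birth that does not exist. The documents do not support that. The rejection figures hold only if birth weight has no true effect and the assumed shares and shifts apply.

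**Data.** A reader might infer that multiple birth will not be recorded. That cannot be concluded either. The claims include diagnosis and billing codes that are not itemised. The Instruments section announces further self-developed questionnaire items with examples only, and the questionnaire is not shown. The causal diagram (Fig. 1) is not shown and may name it. This stands too, but holding a variable does not put it into the model, and the covariate sentence leaves it out.

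**Outcomes.** A reader might take all primary outcomes to be parent-level. They are not: child quality of life is among them and is measured with KINDL. The direct-load argument is made here for parental stress, the parent-child relationship and family quality of life. It is not made for child quality of life, development, utilization or cost, nor for other possible covariates such as birth order, maternal age or smoking in pregnancy.

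**Format.** A condensed article may leave sensitivity analyses to a fuller plan, so the lack of a singleton analysis is no fault in itself. The covariates, however, are not left open: the article names them.

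**Conclusion.** The point holds for the parent and family outcomes. As written, the adjustment set and the matching leave multiple birth uncontrolled, and part of any birth-weight difference in these outcomes may be wrongly read as a consequence of preterm birth. That rests on two premises the documents do not state: multiples are more common below 2,500 g, and raising them affects these outcomes directly. Confidence in the structure is good; confidence in the size is low. Over the assumed range the spurious difference is 0.008-0.09 SD (f 0.004-0.045), with rejection in about 6-82 % of studies under no true effect. It should be corrected because the upper end reaches the detectable effect and the remedy is cheap.

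**What to change.** - Record multiple birth with one questionnaire item, or derive it from the claims data if it is already held there.
- Add it to the covariates stated in the Statistical analysis section, at least for parental stress, the parent-child relationship and family quality of life.
- Repeat those models in singletons.

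**Cost.** One item or derived variable, one covariate and one further model run. At 25 % versus 2 %, adjustment raises the standard error by about 7 % and moves the detectable f from about 0.044 to 0.047. The singleton repeat would keep about 1,950 × 0.75 = 1,462 low-weight children and 3,000 × 0.98 = 2,940 controls. The standard error of their difference grows by √[(1/1,462 + 1/2,940) / (1/1,950 + 1/3,000)] = 1.10, that is 10 %.

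**Timing.** The Instruments section foresees a beta test with revision, so an item can be added if that stage is still open. Questionnaires are dated 2014/2015; if that stage has passed, deriving the variable from claims is the remaining route. The documents do not show that the insurer holds a multiple-birth indicator, and a new data field may need to be checked against the ethics and data-protection approvals.

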### Family-centered care program (FamilieNetz)

Following the increased knowledge about the adverse consequences of preterm birth on child and family, but also on the healthcare system, different psychosocial interventions for parents of preterm infants have been developed with the aim to improve the early parent-child-relationship and reduce parental stress [30–35]. However, existing interventions in Germany are not standardized and have not been evaluated rigorously, making it difficult to draw firm conclusions on their preventive effects [36–38].

A novel support and training program for families of sick newborns and preterm infants (FamilieNetz) was developed and introduced in clinical routine at the Department of Neonatology and Pediatric Intensive Care at the University Hospital Carl Gustav Carus, Dresden in 2009. The comprehensive program consists of different interventions, including parent counseling, parent education and discharge planning. Its philosophy focuses on empowering parents in primary caregiving for their child and involving them in daily routine as early as possible by giving them psychological and social-medical support during the initial hospital stay [39].

Single components of the intervention program have been evaluated and as a consequence health insurance companies in Saxony are compensating it in part since 2012. In a next step, the program shall be introduced into other perinatal centers in Saxony and later in Germany as well. However, prior to the introduction, a comprehensive evaluation of the whole multiple component approach is required, in accordance with the principles of evidence-based healthcare.

In order to address the issues outlined above, the study EcoCare-PIn will examine the following research questions:What are the short- and long-term consequences of preterm birth with regard to parental stress, parent-child relationship, family and child quality of life, child development, and healthcare utilization including costs?Does early family-centered psychosocial care prevent the hypothesized negative consequences of preterm birth on parental stress, parent-child relationship, family and child quality of life, child development, and healthcare utilization including costs?

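### The stated adjustment set omits congenital malformations, so any excess of them at low birth weight would be counted as a consequence of preterm birth

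*Protocol article*

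**What the plan says.** The first research question is causal in wording (Family-centered care program section): "What are the short- and long-term consequences of preterm birth with regard to parental stress", and it goes on to healthcare utilization and costs. The Hypotheses section gives a mechanism: "Preterm birth and subsequent need for medical treatment disturbs the process of postnatal attachment". It lists as secondary outcomes "mental and physical child development (e.g. school performance, comorbidities), healthcare utilization and cost (secondary outcomes").

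The exposure is birth-weight class. Under Methods/Design, because the insurer holds birth weight but not gestational age, the article says "we will use the latter as proxy measure for preterm birth". Under Statistical analysis, the regression models serve "to analyze the effect of birth weight (differentiated into VLBW, LBW and birth weight" of 2,500 g or more). The covariates follow: "Adjustment will be made for sex, year of birth and socioeconomic status".

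Under Design and recruitment, the insurer's data for the whole cohort include "diagnoses (ICD-10 codes), diagnosis related billing information (DRG-codes") as well as procedure codes. Controls for the questionnaire are frequency-matched on birth year, sex and district. Congenital malformations and chromosomal disorders are not mentioned in the text, whether as covariate, matching factor, exclusion or sensitivity analysis.

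**The concern.** A condition that exists before birth, can lower birth weight and independently requires surgery, therapy or repeated admission is a common cause of exposure and outcome. It is not a step on the path from preterm birth through treatment and disturbed attachment, so adjusting for it does not remove the pathway under study. If such conditions are more frequent below 2,500 g, the planned models count the excess as part of the birth-weight effect.

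The proxy adds to this. A term child who is small because of a malformation and weighs less than 2,500 g falls in the group read as preterm, and there is no gestational age in the claims with which to separate that child out.

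At stake is the size of the morbidity, utilization and cost differences that the article intends to hand to health policy. The bias does not shrink as the cohort grows, so almost 140,000 children give no protection.

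**Working it through.** The article has no figure of its own on this point to reproduce. Its power statements concern detectable effect sizes and do not bear on confounding. What follows is arithmetic under stated assumptions.

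**Inputs from the article:** adjustment for sex, year of birth and socioeconomic status; about 1,000 VLBW and 5,500 LBW children among almost 140,000.

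**Assumed inputs (not in the article):** prevalence of major malformation or chromosomal disorder p_C = 3 % in controls and p_L = 6–12 % in a low-weight group; mean cost R = 2 to 5 times higher in affected children, with the same R in both groups.

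**Formula.** With no true birth-weight effect, the ratio of group mean costs is

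(1 + p_L(R − 1)) / (1 + p_C(R − 1)).

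| p_L | R = 2 | R = 3 | R = 5 |
|---|---|---|---|
| 3 % (equal to controls) | 1.00 | 1.00 | 1.00 |
| 6 % | 1.06/1.03 = 1.03 | 1.12/1.06 = 1.06 | 1.24/1.12 = 1.11 |
| 10 % | 1.10/1.03 = 1.07 | 1.20/1.06 = 1.13 | 1.40/1.12 = 1.25 |
| 12 % | 1.12/1.03 = 1.09 | 1.24/1.06 = 1.17 | 1.48/1.12 = 1.32 |

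The range is 1.03–1.32. If there is a true birth-weight effect on cost, then with a common R the factor multiplies it. It applies separately to the VLBW and LBW contrasts, each with its own p_L.

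**Wider assumptions.** With p_C = 2–5 %, p_L two to four times p_C, and R up to 10, the factor runs from 1.04/1.02 = 1.02 to 2.80/1.45 = 1.93.

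**Which part is misattributed.** Only the excess over controls. Of the extra cost of malformations in the low-weight group, the share that enters the contrast is (p_L − p_C)/p_L: 3/6 = 50 % at p_L = 6 %, and 9/12 = 75 % at p_L = 12 %.

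**Children lost by exclusion, same assumptions.** Controls: 133,500 × 0.03 = 4,005. Low weight: 6,500 × 0.06 to 0.12 = 390 to 780. The total of 4,395–4,785 in 140,000 is 3.1–3.4 %, though 6–12 % of the low-weight children.

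**The case against.** The strongest objection is that the bias rests on subject-matter reasoning. The article gives no prevalence, no excess at low birth weight and no cost multiplier. With equal prevalences there is no bias, and the lower end of the range, 1.03, is small. The article also states no expected cost ratio against which to judge it. This stands: the size is conditional, and the point has to be worded that way.

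Second, this is a condensed article. Its covariate sentence does not say that nothing else will be added, and the causal diagram (Fig. 1) is not shown. This carries less weight. The covariates are stated outright, so a reader following the text would fit models without a malformation term.

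Third, the primary outcomes are parental stress, parent-child relationship and quality of life, and nothing here quantifies an effect on them. This stands, and it limits the point to the claims-based secondary outcomes. It does not support demanding the covariate in every model.

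Fourth, a flag built from claims can reflect the intensity of care: children seen more often have more diagnoses coded. In addition, the article's aim is population-based, and an exclusion changes the population described. Both stand and shape the fix.

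Two stronger readings are tempting. A reader might infer that all malformation cost is booked to preterm birth; only the excess over controls is. A reader might also infer that the part preventable by psychosocial care is overstated. The article does not derive preventability from the birth-weight contrast. It models program exposure as its own predictor, with interaction terms, so bias there depends on how malformations divide between exposed and unexposed children. FamilieNetz serves families of sick newborns as well as of preterm infants. If affected children are concentrated in the program, its benefit could be understated. The direction is unknown.

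**Conclusion.** The point holds in conditional form. The stated adjustment set leaves a prenatal possible common cause in a contrast that the article interprets causally, although the diagnosis codes to address it are already supplied. If malformations and chromosomal disorders are more common in the VLBW or LBW groups than in controls, the excess share of their morbidity and cost is attributed to preterm birth.

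The inflation of the cost ratio is 1.03–1.32 under the assumptions of 3 % against 6–12 % and a 2- to 5-fold cost, and 1.00 under equal prevalence. The documents cannot narrow this. The main effect is on comorbidity, utilization and cost. No conclusion is drawn for the program estimate, and an effect on the questionnaire outcomes is possible but not quantified.

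**What to change.** - Pre-specify a flag for major congenital malformations and chromosomal disorders from the ICD-10 codes already delivered. The authors already use ICD-10 codes to reassign children with unknown birth weight (Data preparation), so this fits their workflow.
- Leave out codes for conditions that prematurity itself produces, since these may lie on the causal path.
- Preferably take codes from the birth admission or early infancy. This limits detection bias. It also makes the flag more comparable across birth years, because claims end on 31 December 2013 for children born from 2007 to 2013.
- Report the claims-based VLBW and LBW contrasts with the flag as a covariate, and again without flagged children, next to the planned models in the whole population. Give the flag's prevalence by birth-weight group, which shows directly whether the condition for bias is met.

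The cost is analysis programming on data already held and a code list agreed in advance. Some detection bias may remain in the flag. The exclusion analysis loses a few per cent of children overall (about 3 % under the assumptions above, more among low-weight children) and describes a narrower population, which is why it should accompany the planned models and not replace them.

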### Instruments

The following instruments will be used as part of the primary data collection to assess parental stress, parent-child-relationship, mental development and quality of life. These tests are widely used, valid, reliable, and available in German language:parental stress and parentchild relationshipEBI [Eltern-Belastungs-Inventar] (german version of PSI [Parenting stress index]); Tröster H 2011 [43].mental development of childrenSDQ [Strengths and Difficulties Questionnaire]; Goodman R 1997 [44].quality of lifeparents: WHOQOL-BREF [WHO-Quality of Life—brief version]; Angermeyer MC et al. 2000 [45].children: KINDL [Questionnaire for the collection of health-related quality of life in children and adolescents]; Ravens-Sieberer U, Bullinger M 1998 [46].

These instruments are incorporated into the study questionnaire after having obtained the respective author licenses. At the timepoint of submission of this study protocol, all necessary licenses had been obtained.

To meet the goal of assessing potential consequences of preterm birth not covered with these instruments (e.g. school performance, details on physical development) as well as details on psychosocial care in the neonatal period, the study questionnaire will also contain items developed by the authors and the scientific advisory board. The study questionnaire will be beta-tested and revised if necessary prior to application.

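### The birth-weight models control for only one family-level factor, socioeconomic status, so maternal factors that precede the birth can confound the estimated effect of preterm birth on parental outcomes

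*Protocol article*

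**What the plan says.** The Statistical analysis section plans regression models "to analyze the effect of birth weight (differentiated into VLBW, LBW and birth weight ≥ 2,500 g) on the outcomes". It then gives one adjustment list: "Adjustment will be made for sex, year of birth and socioeconomic status".

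The Hypotheses section is worded causally. Preterm birth and the treatment that follows "will have an impact on (I) parental stress, parent-child-relationship, and quality of life of family and child at age 1–7 years (primary outcomes"), and a hypothesized causal model is cited as Fig. 1, which is not shown. The Instruments section measures parental stress and the parent-child relationship with a parent stress inventory, and parents' quality of life with a parent-completed scale.

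The Design and recruitment section contains three relevant statements:

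- Control selection: "Control children for the primary data collection will be selected via frequency matching according to birth year, sex and administrative district". No maternal factor is used.
- Claims data: "selected sociodemographic characteristics of children (age, sex, first three digits of ZIP code"). These are attributes of the child.
- Questionnaire: it covers, among other topics, "sociodemographic characteristics of parents, and exposure to psychosocial care in the neonatal period".

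Under Instruments, "the study questionnaire will also contain items developed by the authors and the scientific advisory board", and the form is to be beta-tested and, if needed, revised before use.

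**The concern.** The stated list is short for a causal question about parents. Sex and year of birth describe the child. Only socioeconomic status describes the family. Maternal age, smoking in pregnancy and mental illness before the birth all precede the exposure. Each can plausibly affect both birth weight and the stress or quality of life that a parent reports years later. None is a consequence of the birth, so in principle, with accurate measurement, adjusting for them would not take away any of the effect under study.

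No visible section deals with such factors by matching, restriction, adjustment or sensitivity analysis, and the visible text does not acknowledge residual confounding. At stake is the answer to the first research question on the primary outcomes: a difference between birth-weight groups could be credited to preterm birth when part of it was present before. The linked analysis is sized for very small effects, so a small residual imbalance can matter.

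**Working it through.** **Inputs from the protocol article.** About 1,000 VLBW children, 5,500 LBW children and 10,000 controls are approached (Design and recruitment). The expected response is 30 %, power 80 %, significance level 5 %, detectable Cohen's f 0.045 in the linked dataset (Statistical analysis).

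**Step 1: responders.** 0.30 × 1,000 = 300 VLBW; 0.30 × 5,500 = 1,650 LBW; 0.30 × 10,000 = 3,000 controls. Total N = 4,950, of whom 1,950 are below 2,500 g.

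**Step 2: the plan's own figure.** F test for three groups, 2 numerator degrees of freedom, noncentrality f² × N = 0.045² × 4,950 = 10.02. Power is 81.6 %, and the smallest f detectable at 80 % power is 0.0441. The stated 0.045 is reproduced.

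**Step 3: f in SD units.** If VLBW and LBW differ equally from controls, f = d × √(0.394 × 0.606) = 0.489 d, with 0.394 = 1,950/4,950. So f = 0.045 corresponds to d = 0.045/0.489 = 0.092 SD.

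**Step 4: bias from one omitted binary factor.** Bias in SD = (difference in prevalence remaining after adjustment for socioeconomic status) × (effect of the factor on the outcome in SD). The document gives neither quantity. Assumed ranges: 3-10 percentage points and 0.3-0.8 SD, with the same gap for VLBW and LBW.

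**Step 5: chance of a significant result with no true effect.** Convert the bias to f (× 0.489) and use the test of step 2.

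| Prevalence gap | Effect (SD) | Bias (SD) | f | Share of 0.092 SD | Rejection of a true null |
|---|---|---|---|---|---|
| 3 points | 0.3 | 0.009 | 0.004 | 10 % | 6 % |
| 5 points | 0.5 | 0.025 | 0.012 | 27 % | 11 % |
| 10 points | 0.5 | 0.050 | 0.024 | 54 % | 32 % |
| 10 points | 0.8 | 0.080 | 0.039 | 87 % | 69 % |

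The nominal rate is 5 %. The low end is close to harmless and the high end is not.

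**The case against.** The strongest reply is that a condensed article puts all outcomes, two datasets and both research questions into one paragraph, and that wider covariate sets and sensitivity models often sit in a full protocol or analysis plan. That would answer a complaint about silence. Here a list is stated, without any sign that it is only an example, so the objection is to a stated choice.

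Several other points stand and limit the claim:

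- **Size.** Prevalence gaps and effects are assumptions. Adjustment for socioeconomic status removes part of any confounding by maternal age and smoking, and nothing in the document says how much is left. A reader might infer that the preterm effect is shown to be materially biased. A range from 6 % to 69 % does not show that.
- **Test used.** Pooling VLBW and LBW into a single contrast would raise the upper end to about 79 %. The planned models separate three groups, so the lower figures apply.
- **Matching.** A reader might conclude that sex and birth year are idle terms because controls are matched on them. Frequency matching balances those approached, not the 30 % who respond, and does not apply to the whole-cohort analyses. Those terms should stay.
- **Measurement.** Births are from 2007-2013 and the questionnaire is from 2014/2015. Recall of smoking or earlier illness may differ by birth outcome or current stress, and the respondent may be a father or another legal caregiver. It is therefore too strong to say that adjusting for recalled answers can only help.
- **Unseen material.** Neither Fig. 1 nor the questionnaire is shown. It cannot be said that smoking or prior illness is not collected, only that neither is named.

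**Conclusion.** The point holds as a weakness in a stated analysis choice. With the listed covariates, socioeconomic status alone carries the control for family differences, while the claim is causal and the primary outcomes are largely the parent's own state. Pre-birth maternal factors can therefore confound the estimate.

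How far they do so is unknown. The figures of 0.009-0.08 SD and about 6-69 % false rejection are conditional on the assumed gaps and effects, on a single binary factor, on equal shifts in both low-weight groups and on the expected 30 % response. They show that an analysis able to detect about 0.09 SD can also declare a modest confounded difference significant. They do not show that such a difference exists.

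The document also does not support the stronger conclusion that all three maternal factors belong in the main model. Maternal age is a reasonable addition there. Smoking and earlier mental illness, recalled years later and perhaps not by the mother, belong in a sensitivity model.

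**What to change.** 1. In Statistical analysis, add maternal age at birth to the adjustment set of the linked-data birth-weight models, alongside sex, year of birth and socioeconomic status. Take it from the parental sociodemographic items, and make sure these ask for the mother's age or year of birth whoever responds.
2. Before the beta test, add short items on smoking in pregnancy and on maternal mental illness before the birth. Use them in a sensitivity model stated in advance and reported beside the main model, with the reason given: possible differential recall and respondents who are not the mother.
3. State that the whole-cohort claims results are associations not adjusted for maternal factors, since the listed claims fields describe the child.

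The cost is two or three questionnaire items and a few model terms. Longer or more sensitive questions could slightly affect a response already expected to be only 30 %. Imperfect recall leaves residual confounding and may add recall bias, so the sensitivity model informs the interpretation but does not settle it.
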